
This trial will last 6 months, and data will be collected at baseline, 3-month follow-up and 6-month follow-up (the end of the intervention), respectively (seeing Fig. 2 for flow diagram).

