### Sample size

We estimate the intervention will achieve an improvement of the primary outcome, i.e., ‘rate of effective utilization of PPE during the last week’ by 43 for top-down intervention arm and 53 % for comprehensive intervention arm. According to our previous study, among migrant workers exposed to organic solvents in SMEs, the rate of effective utilization of PPE was16.8 % [10]. Based on a pilot study we did in three SMEs in Guangzhou in 2014, we expected the rate will be increased to reach 60 and 70 % in top-down and comprehensive intervention arm, respectively. Based on an estimated intra-class correlation coefficient (ICC) of 0.05(previous literature reported that ICCs for participants’ behaviours and intent to change those behaviours were generally less than 0.1 [36]), an alpha of 0.05(one-side) and a beta of 0.20, we need 684 samples and 54 enterprises. We estimated the dropout rate will be 20 % as our exploratory study showed that annual turnover rate of migrant workers exposed to organic solvents in study SMEs was 26 %. In addition, considering that SMEs are sensitive to economic depression and based on experience of local administration of work safety, we also estimated 10 % of study SMEs may close down during intervention period. Therefore, we aim to recruit a total of 60 enterprises (20 for each arm) and at least 920 migrant workers.

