### Data analysis

We will follow CONSORT guidelines [37, 38] to analyse and present the data. Intention-to-treat (ITT) analyses [39] will be used to estimate effectiveness of intervention. Therefore, all SMEs and migrant workers that are initially randomized and provide data at baseline will be included in the analysis. Migrant workers missing at baseline but present at follow-up surveys will be excluded from the ITT analyses.

The analysis will be conducted at the individual level. The baseline characteristics, e.g. demographic characteristics, occupational health knowledge and attitude and PPE utilization behaviour, of migrant workers will be described using mean (standard deviation), median (interquartile range) or proportions as appropriate and compared across three arms. Generalized estimating equations (GEE) will be used for the primary outcome adjusted for baseline PPE utilization behaviour to evaluate the effectiveness of intervention. A sensitivity analysis will be undertaken to adjust for the number of intervention sections received during the trial, which will be calculated based on general health educators, peer education group leaders and migrant workers’ feedback. In addition, subgroup analyses by migrant workers’ sex, age and education status, and SMEs’ occupational health practice, e.g. occupational health supervision, will be performed. For the secondary outcomes, linear mixed effects models will be applied for occupational health knowledge and attitude and GEE will be used for participation in occupational health check-up. Results from all secondary analyses will be treated as exploratory and presented as estimates with confidence intervals.

Although drop outs are expected, missing data will not be imputed. Because GEE and linear mixed effects models assume that missing data are missing at random. Under this assumption, the complete-case analysis by including predictors of missing observations will provide consistent estimates of the parameter [40].

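### No imputation is justified by saying GEE assumes missing at random; unweighted GEE does not cover drop-out related to 3-month PPE use, and the promised analysis set does not fit a complete-case analysis

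*Protocol article*

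**What the plan says.** All of the analysis text is in the protocol article, Methods/Design, Data analysis.

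- Primary model: "Generalized estimating equations (GEE) will be used for the primary outcome adjusted for baseline PPE utilization behaviour". No weighting is mentioned. GEE is also the method for check-up participation; linear mixed models are used for knowledge and attitude.
- Missing data, decision and reason together: "missing data will not be imputed. Because GEE and linear mixed effects models assume that missing data are missing at random". A qualifier follows: under that assumption "the complete-case analysis by including predictors of missing observations will provide consistent estimates of the parameter".
- Analysis set, under the intention-to-treat label: "all SMEs and migrant workers that are initially randomized and provide data at baseline will be included in the analysis".

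Elsewhere, the text closing Study interventions says that "data will be collected at baseline, 3-month follow-up and 6-month follow-up (the end of the intervention"). Sample size says "We estimated the dropout rate will be 20" per cent and allows for 10% of enterprises closing.

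**The concern.** The article treats GEE and linear mixed models as equivalent under missing at random (MAR) and rests a fixed decision, no imputation, on that. They are not equivalent. A correctly specified likelihood model uses a worker's observed 3-month value when the 6-month value is missing. Unweighted GEE in general does not make that correction.

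If workers who are not using PPE at month 3 are more likely to leave before month 6, those who remain over-represent users. If this happens to a different degree in different arms, the treatment contrast shifts, while the report would cite MAR as its protection. Separately, readers would be told that everyone with baseline data was analysed when a sizeable fraction contributed no outcome.

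**Working it through.** The article gives no bias figure to reproduce, so the check is of the stated principle, then of its possible size.

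**Inputs from the article (Sample size):** expected rates 16.8% (control), 60% (top-down), 70% (comprehensive); worker drop-out 20%; enterprise closure 10%; at least 920 workers. **Assumed, because the article gives nothing:** how drop-out splits between PPE users and non-users, and the correlation of PPE use across visits.

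**Step 1: the condition.** With response Y, covariates X, mean model μ(X) and R = 1 if Y is observed, unweighted GEE under working independence is consistent if E[R(Y − μ(X)) | X] = 0. That holds if R is independent of Y given X. If R at month 6 depends on 3-month PPE use, and 3-month use predicts 6-month use beyond X, the condition fails although the data are MAR.

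**Step 2: what conditioning covers.**
- Baseline PPE use: covered, since it is in the model.
- Other measured baseline predictors: covered if the qualifier is carried out.
- 3-month PPE use: not properly covered. It is measured after the intervention starts and repeats the primary outcome. Adjusting for it would change the effect being estimated.

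**Step 3: hand illustration, no covariates.** Suppose 60% use PPE at month 3, and 80% of those users and 30% of the non-users use it at month 6. The true 6-month rate is 0.6×0.8 + 0.4×0.3 = 0.60. Let 10% of users and 35% of non-users leave. Overall loss is 0.6×0.10 + 0.4×0.35 = 0.20, the planned figure. Among those remaining:

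(0.6×0.9×0.8 + 0.4×0.65×0.3) / (0.6×0.9 + 0.4×0.65) = 0.510/0.80 = 0.6375.

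The arm is overstated by 3.75 points. If another arm with the same true rate loses a flat 20%, the contrast is off by that amount. If both arms share the mechanism, most of it cancels.

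**Step 4: planned rates, adjusted for baseline use.** Large-sample simulation, available cases, latent between-visit correlation 0.3 to 0.7, drop-out 10% in users and 30% in non-users, widened to 5% and 40%. True differences are 60 − 16.8 = 43.2, 70 − 16.8 = 53.2 and 70 − 60 = 10 points.

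| Drop-out depends on | Top-down v control | Comprehensive v control |
|---|---|---|
| Baseline use | about 43 (no bias) | about 53 (no bias) |
| 3-month use, all arms | 43.7 to 45.4 | 53.5 to 55.1 |
| 3-month use, intervention arms only | 44.2 to 47.2 | 54.0 to 56.9 |

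In the last two rows the bias is about +0.3 to +2.2 and +1 to +4 points. Comprehensive versus top-down stays at 9.5 to 10.0, because both arms were given the same mechanism.

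**Step 5: mechanism in one of two otherwise equal arms, and the working correlation.** With the Step 3 drop-out rates in one arm and a flat 20% in the other, GEE with independence or enterprise-level exchangeable correlation gave a spurious difference of roughly 2 to 4 points across separate simulations. In one of these, inverse-probability weighting on 3-month use returned 0.3 points, equal in size to the gap between the simulated true rates (59.7% and 59.4%). Exchangeable correlation within worker cut the bias to 0.7 points or less. In a control versus top-down case with flat loss in control it only reduced it, from about +3.8 to +2.0.

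**Step 6: the analysis set.** A worker with baseline data and no follow-up has no response to enter in a baseline-adjusted model. Read literally, complete-case analysis would also drop a worker who missed one follow-up. If drop-out and closure are independent, loss is 1 − 0.8×0.9 = 0.28, and 0.28×920 = 257.6, so about 258 baseline workers could lack the 6-month outcome. Including all of them and imputing nothing cannot both hold in an unweighted complete-case model.

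**The case against.** The strongest case for the plan runs as follows. The authors do not rely on a bare MAR claim: the next sentence requires predictors of missingness in the model, which is close to the condition GEE needs. The primary model already contains baseline PPE use. Sample size attributes expected loss to ordinary staff turnover and economic closures, not to PPE behaviour, and Data management has reasons for loss recorded. The working correlation, which matters for the bias, is a detail an article may leave to the analysis plan. Effects of 43 and 53 points would survive any of the biases shown.

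Much of this stands and limits the point. Two stronger readings should be resisted.

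- A reader might infer that the primary effect is biased whenever drop-out depends on earlier PPE use. The article does not support that: dependence on baseline use is handled by the stated adjustment, and only dependence on 3-month use, given baseline, is left open.
- A reader might infer a bias approaching 4 points in the comprehensive versus top-down contrast. That needs a mechanism confined to one active arm and a working correlation that ignores repeated measures within worker. The article states neither. Teaching about solvent hazards is common to both active arms. A difference between them is conceivable, since only the comprehensive arm has peer leaders monitoring PPE use, but it remains an assumption.

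What the objection does not rescue is the sentence itself. The decision not to impute is fixed on a property that unweighted GEE lacks, and the qualifier does not properly reach 3-month PPE use. Nor does it reconcile the promised set with a complete-case analysis.

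**Conclusion.** The concern holds in this limited form. The MAR justification is right for the linear mixed models and wrong for unweighted GEE. The primary contrast may be biased under MAR if drop-out depends on 3-month PPE use. The size is about 0 to 4 percentage points under the assumed drop-out splits and correlations, depending on the working correlation and on whether the mechanism differs by arm. This would not overturn the planned effects versus control. It could matter for the second aim, the 10-point comparison of the two interventions, if drop-out differs between those arms.

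The contradiction over the analysed set follows from the text alone and needs no simulation; only the figure of about 258 workers assumes independent losses. Confidence is high on the wording error and the contradiction, lower on magnitude. Severity: should be fixed, before analysis.

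**What to change.** 1. Remove the statement that GEE is valid under MAR; keep it for the linear mixed models only.
2. Make the primary analysis valid under MAR with data already being collected. Two options: weighted GEE, with observation weights modelled from arm, baseline covariates and 3-month PPE use; or multilevel multiple imputation by arm, with enterprise effects and 3-month PPE use in the imputation model, followed by the same GEE. A likelihood-based mixed logistic model is a further possibility, but its effect is conditional on the random effects, so the estimand should then be stated.
3. Keep the unweighted, baseline-adjusted GEE as a sensitivity analysis.
4. Describe the analysed set accurately: all workers with baseline data if weighting or imputation is used, otherwise workers with at least one follow-up outcome.

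Cost: revised wording, modest programming and slightly wider intervals. No new data are needed.

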## Discussion

Migrant workers are one of the main sources of labor force and a vulnerable group for occupational health. To our knowledge, this is the first behavioural intervention programme targeting PPE utilization of migrant workers exposed to organic solvents in SMEs in China. Our intervention is based on theoretical models, previous exploratory study and participants’ feedback. This study will contribute to the limited evidence on behavioural intervention for occupational health prevention in SMEs [23]. Our study will also contribute to the evidence base of developing basic occupational health services in China and elsewhere with similar industrialization contexts. In addition, this intervention has good replicability as they can be implemented by migrant workers themselves with relatively low cost. Ensuring the fidelity of a complex intervention is challenging, although we have developed stringent monitoring and reporting system. Sustaining the effects of behavioural change intervention will also be difficult. However, this problem will be mitigated given this is a theory-based pragmatic trial that also aims to strengthen the capacity of enterprise managers and workers.

## Abbreviations

GDP, Gross Domestic Product, GEE, Generalized Estimating Equations, ICC, intra-class correlation coefficient, ITT, Intention-to-treat, PPE, Personal Protective Equipment, RCT, Randomized Controlled Trial, SMEs, Small and Medium-sized Enterprises
